### Recruitment of schools

The intervention program is school-based, and was carried out among children in the third, second and third grade classes by teachers and among school staff by principals. All Finnish primary schools had the opportunity to participate if the school had a minimum of two teachers who agreed to participate for the whole study period of two years. As a part of the recruitment of schools and teachers, an advertisement was published in the national Teacher-journal informing about the study aims and core ideas. The actual recruitment process began in autumn 2012 by sending invitation letters to all Finnish primary schools welcoming participation to the study. The invitation letter included information on the study aims (i.e. promoting children’s mental health by teaching socio-emotional skills in schools) and eligibility criterion. The recruitment process ended at the end of November 2012 and resulted in 109 schools that were willing to participate of which 86 schools met the eligibility criteria.

### Randomization of schools

Schools that met the eligibility criteria were randomly assigned into either intervention or control groups (Figure 1). The schools in the two groups were evenly distributed geographically (east/west) between rural and urban schools. After randomization, the schools were contacted by mail and the upcoming study procedures regarding e.g. study groups and timelines were explained in detail. Before randomization 23 schools were excluded due to a contamination risk (5 schools from the town of Ylöjärvi where the program was developed in close cooperation with the schools, and 1 pilot study school), or due to excessive training costs (13 very small schools and 4 remote rural schools).

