### Sample size

Power analyses were conducted to estimate the required sample size. The starting point for calculations was a multilevel model comprising two levels: school and pupil. It was assumed that 2-5 classes (typically 2-3) would participate per school, one class containing 20 pupils, the recruitment rate being 70% and attrition 10% during the follow-up. Calculations based on these assumptions resulted in a total of 25 (2*20*0.7*0.9) to 63 (5*20*0.7*0.9) children per school. The intra-cluster correlation coefficient (ICC) between schools for the primary outcome measure (SDQ total difficulties score) was assumed to be 0.15 [13] and the effect size between the intervention and control groups was expected to be a) 0.25 or b) 0.3. This is in line with corresponding research where the effect size has been found to vary between small and moderate [4, 9]. In a two level design using a significance level of 0.05 and requiring 80% power a sample size of a) 2400-5355 children (i.e. 96-85 schools) or b) 1675-3780 children (i.e. 67-60 schools) is required. Based on these calculations we decided to recruit 100 schools into the study. Sample size calculations were undertaken using Optimal Design Software [14].

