### Plan of statistical methods

Because of a clustered data structure, random effects linear regression models are applied to compare the means for continuous outcomes between the trial arms and generalized linear mixed models or generalized estimating evaluation (GEE) models to compare binary outcomes (e.g. borderline/abnormal versus normal status on the SDQ). Analyses are adjusted for important prognostic factors e.g. child gender, year group, and a baseline SDQ score. Stratified analyses according to year group will be performed.

The dataset will be preprocessed prior to the analysis and missing data will be handled properly. Imputation techniques will be used when necessary. Demographic and baseline characteristics will be summarized using means and standard deviations (or medians and inter-quartile ranges) for quantitative variables and percentages for categorical variables. Possible differences in the intervention effects between subgroups will be investigated in secondary analysis. These subgroups are formed based on SDQ scores and family socio-economic status.

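### Region and rural/urban, on which the school allocation appears to have been balanced, are not among the covariates named for the arm comparisons; adding them costs almost nothing and may recover some precision

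*Protocol article*

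**What the plan says.** Under Randomization of schools, the article reports that eligible schools were assigned at random to two arms and adds: "The schools in the two groups were evenly distributed geographically (east/west) between rural and urban schools". It does not use the words stratified, blocked or restricted. Under Drop-out schools, 3 intervention and 4 control schools left after randomisation and 40 and 39 remained, so 43 were allocated to each arm.

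Under Plan of statistical methods, "random effects linear regression models are applied to compare the means for continuous outcomes between the trial arms", with generalised linear mixed or GEE models for binary outcomes. On covariates: "Analyses are adjusted for important prognostic factors e.g. child gender, year group, and a baseline SDQ score". On strata: "Stratified analyses according to year group will be performed". Region and rural/urban are not mentioned in that section.

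Under Sample size, the calculation is a two-level one with a between-school ICC of 0.15, and "the effect size between the intervention and control groups was expected to be a) 0.25 or b) 0.3". It uses no covariates and no blocking, so it claims no precision from the balancing.

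**The concern.** Factors used to balance an allocation normally belong in the analysis model. Balancing removes their contribution from the chance difference between the arms. If the model omits them, their variance stays in the school-level error term, and the reported standard error exceeds the true sampling variability of the arm contrast. Confidence intervals are then too wide and the test rejects less often than its nominal level.

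This deserves attention here because the school is the unit of randomisation and most of the variance of the arm contrast lies between schools. The trial also has fewer schools (79) than the 85 to 96 that the article's own calculation requires for an effect of 0.25. None of the three covariates named as examples is a school-level allocation factor.

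**Working it through.** **Inputs.** From Sample size: ICC ρ = 0.15, effect d = 0.25 or 0.30, n = 25 to 63 children per school, significance level 0.05 (taken as two-sided), power 80%. From Drop-out schools: J = 79. Assumed, because the article gives no figure: R², the share of between-school variance explained by region and rural/urban; and S, the share of variance at both levels explained by baseline SDQ.

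**1. The article's own figures.** Noncentral F with 1 and J − 2 degrees of freedom, λ = J·d² / (4·[ρ + (1 − ρ)/n]). For d = 0.25 and n = 25: ρ + (1 − ρ)/n = 0.15 + 0.034 = 0.184, and λ = 96 × 0.0625 / 0.736 = 8.15, which gives power 0.807. The smallest J reaching 80% is 95, 85, 67 and 60, against the stated 96, 85, 67 and 60. The calculation reproduces.

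**2. Power with 79 schools and no covariates, d = 0.25.**
- n = 25: λ = 4.9375 / 0.736 = 6.71, power 0.725.
- n = 63: the bracket is 0.15 + 0.0135 = 0.1635, λ = 4.9375 / 0.654 = 7.55, power 0.774.
- Between-school share of the variance of a school mean: 0.15/0.184 = 82% to 0.15/0.1635 = 92%.

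**3. Adding the two factors.** Replace ρ by ρ(1 − R²) in the bracket and use J − 4 degrees of freedom. For R² = 0.10 and n = 25 the bracket is 0.135 + 0.034 = 0.169, so the standard error ratio is √(0.169/0.184) = 0.958.

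| R² (assumed) | SE ratio, n = 25 / 63 | Power at 0.25, n = 25 / 63 |
|---|---|---|
| 0 | 1.00 / 1.00 | 0.725 / 0.774 |
| 0.05 | 0.98 / 0.98 | 0.742 / 0.793 |
| 0.10 | 0.96 / 0.95 | 0.760 / 0.812 |
| 0.20 | 0.92 / 0.90 | 0.798 / 0.851 |

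**4. Size of the test if allocation was balanced and the factors are omitted.** The effective critical value is 1.991 (t, 77 df) divided by the SE ratio. For R² = 0.10 and n = 25 it is 1.991/0.958 = 2.078, a true two-sided level of 0.041. Over n = 25 to 63 the true level is about 0.045 (R² = 0.05), 0.040 to 0.041 (R² = 0.10) and 0.031 to 0.033 (R² = 0.20).

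The first row of the table is the covariate-free planning power. Under balanced allocation the conservative test does slightly better than that row, because the true standard error is smaller. For R² = 0.20 and n = 25, 0.25/0.0883 − 1.991/0.915 = 2.83 − 2.18 = 0.65, a normal probability of about 0.74. In that case the gain from adding the factors is nearer 5 points than 7.

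**5. After baseline SDQ adjustment.** Multiply both variance components by 1 − S, with n = 44 (midpoint of 25 and 63). For S = 0.30 and R² = 0.20 the bracket is 0.7 × (0.12 + 0.0193) = 0.0975, λ = 4.9375/0.390 = 12.66, power 0.940.

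| S (assumed) | Without the factors | R² = 0.10 | R² = 0.20 |
|---|---|---|---|
| 0 | 0.760 | 0.797 | 0.836 |
| 0.30 | 0.890 | 0.916 | 0.940 |
| 0.50 | 0.965 | 0.977 | 0.986 |

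Here R² is the share of what remains between schools after SDQ. With S between 0.30 and 0.50 the gain is about 1 to 5 points. It is nil if SDQ has already absorbed what the factors explain.

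**The case against.** The strongest objection is that nothing in the article excludes the two factors. A reader might infer that the analysis adjusts only for gender, year group and SDQ, but the sentence introduces these with e.g., so the list is open. A journal article may also leave the full covariate list to an analysis plan that is not shown. This stands: the article does not name the factors, and no more than that can be said.

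A reader might also infer that allocation was stated to be stratified. It was not; the sentence could describe the result of the draw. Its place under the randomisation heading, directly after the assignment, and the exact 43/43 split make balance by design the natural reading. The split alone does not prove it, since a fixed-size draw would give the same numbers. Under simple randomisation the unadjusted test keeps its nominal level.

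A third inference, that only school-level covariates can recover power here, is wrong. Baseline SDQ also varies between schools and is among the covariates named. For that reason the rise from 0.76 to between 0.80 and 0.84 at 44 pupils cannot be read as the expected gain: it compares against a covariate-free model, which is not the planned analysis.

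What survives is that the covariates actually named include no allocation factor, and that naming both is a concrete and nearly free improvement.

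**Conclusion.** The point holds as a modest, low-cost improvement; it is not an error that threatens validity. If balance was imposed by design and the factors predict outcome, fitting only the named covariates gives standard errors that are too large and a conservative test. The linear-model estimate is not biased and the type I error is not inflated.

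The size cannot be derived from the article. Against a covariate-free model, an assumed R² of 10 to 20% brings power at 0.25 from 0.73–0.77 to between 0.76 and 0.85. Against the baseline-adjusted model that is planned, the gain is smaller and may be nil. No stated figure is contradicted, because the sample size calculation takes no credit for the balancing. Confidence is moderate, because the balance by design is inferred and R² is assumed.

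**What to change.** State whether east/west and rural/urban were used to restrict the allocation. Include both, coded as used in allocation, as fixed effects in every arm comparison: the linear random-effects models, the GLMMs and the GEE models. If allocation was within the four region-by-urbanicity cells, include their interaction. Fix this in the analysis plan before the outcome comparisons are run.

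The cost is 2 school-level degrees of freedom, or 3 with the interaction, out of 77. With R² = 0 this changes power by less than 0.1 point. No new data collection should be needed, since both are school characteristics that the article already reports as evenly distributed between the arms. In the logistic models the odds ratio becomes conditional on the two factors and should be labelled as such.

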### Drop-out schools

As outlined in Figure 1, a total of 7 schools (3 intervention and 4 control) declined their participation after the randomization (4 in April 2013, 2 in August, 1 in September 2013) due to various reasons (e.g. school economic situation, personnel shortage). After drop-outs a total of 79 schools (40 intervention and 39 control), 79 principals and 257 teachers (with 4802 children) participated in the trial.

### Participants and consent procedure

#### Recruitment of the children and consent procedure

All children from the intervention classes received the intervention as the intervention was integrated into the normal school curriculum. The control schools participated in the data collection of the study. All parents of the participating classes received an information letter regarding the intervention program, the study project and data collection of and by their children. The information letter also included a consent form for data collection. The letter was sent in two waves, in spring 2013 for those children who had already started school (second and third grade in autumn 2013), and in autumn 2013 for the children who started their school (first grade). The parents’ consent procedure regarding the data collection on themselves and their children is outlined below more in detail. The teachers and principals gave their consent to the data collection regarding themselves by answering the teacher questionnaire (also including school and class level information).

The consent regarding the children’s participation in the data collection was threefold and asked for the parents’ consent for (a) the child completing the computer based assessments in school including different tasks and multiple choice questions, (b) the teacher’s evaluation of the child and school-parent collaboration, and (c) the parents’ own evaluation of their child and school parent collaboration. The parents were asked to answer yes/no to all the above mentioned consent items. Before answering the parents were told to explain the content of the study and information letter to their child so that the child would have the opportunity to decline completing the computer based assessments. The child could also refuse to complete the assessments in the actual test situation if he/she wanted. Apart from the two official languages (Finnish and Swedish), the consent form was available in English, Estonian, Russian, Somali, Albanian, Arabic and Chinese which are the most frequent foreign languages in Finland and in the study schools.

The teachers distributed and collected the parental consents via the children in sealed envelopes. The initial collection was followed by two reminding letters which resulted in an additional 106 consents. All in all, parental consent forms were returned for 4462 children (93%) of the total number of 4802 children in the participating school classes. Of the returned forms, 89% of the children received parental consent to all data collection (n = 3990), 84% for the children to complete the children’s assessments, 86% for the parent’s evaluation of their child, and 87% for the teacher’s evaluation of the child. As a whole, 82% children received parental consent to all three consents (their child’s participation along with the teachers and their own evaluation of their child), and 11% declined all three consents. There was no major difference in the concerting proportions between the intervention and control groups (Figure 1).

### Intervention

A synopsis including brief descriptions of the intervention methods and tools is outlined in Additional file 1. The methods and tools can be divided into three groups: class methods for the children carried out by the teachers, work environment methods for the school staff carried out by the principal and the staff, and teacher-parent collaboration methods carried out by the teachers. The class methods include: Circle time, Do it Myself -lesson and Do it Together -lesson, and individual discussion between the teacher and the child and material for the starting of the school year. The work environment methods are: Planning of Collaborative Time, Staff Meeting, Service Station, and Toolkit Session which are also designed to ameliorate and strengthen school development. The methods designed for teacher-parent collaboration are: materials for meeting the parents individually and as a group (Parents Evening). All methods and tools are described in a detailed intervention program Together at School manual (258 pages). The manual includes methods, tools and instructions for the teaching staff regarding pupil tutoring, teacher- parent collaboration, and working together as a staff. The intervention group teachers receive the manual during their training period and the control schools will receive the same manual after the last measuring point (T_2_ in spring 2015).

The teachers of the control schools were offered two lectures on socio-emotional skills (2 × 3 hours, altogether 6 hours). The first lecture was held in November 2013 and the second in March 2014 as described in Table 1.

### Intervention development

The development of the intervention program took place in three schools in the town of Ylöjärvi. A group of teachers, principals, and health care professionals participated in the development process. The process lasted for eight years during which the intervention tools and methods were regularly tested, modified and adopted in close collaboration with three development schools. The teachers and children tested the materials in classrooms while the principals tested the materials among the staff. The pilot study was conducted in four schools (in two different towns, Raisio and Vantaa) in 2011-2012. The results of the pilot study showed that the intervention program was feasible, i.e. the intervention can be considered as safe with no significant negative impact, and the teachers deemed it as suitable and effective in the different school settings [15].

### Intervention delivery

The intervention group teachers received an intervention training which extended over 10 months (from March 2013 till March 2014, excluding 3 summer months). The training period of the intervention program was divided into 4 modules (Table 1). Altogether 138 teachers and 40 principals participated in the training. Also other members of the school staff were allowed to participate. The teachers received 3 and principals 2 lectures including exercises and group discussions. The components of the training varied somewhat depending on the target group (teacher, principal, or the whole staff). In addition, every intervention school teachers and principals were visited 4 times at their own schools to support the use of Together at School methods. In conjunction with these visits the whole school staff received 4 lectures on how to improve their work environment with the intervention methods.

The intervention training group consisted of six instructors. The training of the program was divided among three instructor pairs, i.e. the instructors worked as a pair taking turns so that when one of the instructors was lecturing, the other was observing. After each training module the teachers started to use the tools and methods by their own in their own classes and the principals in their school communities.

At the end of the training of intervention program the teachers filled in a questionnaire regarding satisfaction with the methods and training of the intervention program. The questionnaire was distributed and filled in at the end of the last training day. The teachers in the control group received a similar questionnaire by mail.

### Intervention integrity

Intervention integrity refers to the extent to which the intervention is implemented as intended see e.g. [16]. In the present study subsequent steps were followed in order to ensure treatment integrity. Before the intervention delivery the teachers were trained and supervised by six instructors (trained teachers and intervention developers with a degree in pedagogics) and provided with detailed intervention materials. The teachers completed both detailed intervention protocols that specified the amount of and content of each session (e.g. dosage) along with protocol adherence checklists. Furthermore, the intervention materials were discussed between the instructors and teachers during individual trainer-teacher school meetings as a part of the intervention training process. Altogether, the aim of these meetings were to ensure an adequate skill and competence level, proper utilization of the intervention material and methods and intervention differentiation (intervention differs from other interventions with the regard to critical dimensions).

### Measures

The study was designed to evaluate children’s socio-emotional skills and mental health as primary outcomes, and related underlying mechanisms (i.e. emotional understanding, altruistic behavior, and executive functions) along with school and family related factors as secondary outcomes.

Also background information was collected from the teachers (regarding their own class and their professional background information), the principal (regarding their own class and/or professional and school background information), and parents (regarding family background information). Apart from the background information, a description of all measures used in the data collection is reported in Table 2.

**Table 2 Tab2:** **Outcome measures**

Outcome measures		Informant		
Primary outcomes		Child	Teacher	Parent
**Children**				
Psychological problems (conduct disorder, hyperactivity, emotional problems)	Strength and difficulties questionnaire (SDQ)		x	x
Socio-emotional skills (prosocial behaviors, peer relations)	Strength and difficulties questionnaire (SDQ)		x	x
Socio-emotional skills (prosocial skills)*****	Multisource Assessment of Social Competence Scale (MASCS)		x	x
**Secondary outcomes**				
**Children**				
Emotional understanding of different situations and behaviours	Assessment of Children’s Emotion Skills (ACES)	x		
Emotional processing and recognition of facial expressions	The diagnostic analysis of nonverbal accuracy 2 (DANVA2-CF)	x		
Altruistic behavior (other regarding preferences)	The Dictator Game	x		
Executive functions. Working memory	Adaptation of Block Tapping Test	x		
Executive functions: Planning	Adaptation of Tower of London	x		
Executive functions: Inhibition	Go/No-Go - task	x		
Socio-emotional skills	Measure designed for the intervention study	x		
Depressive symptoms	Children’s Depression Inventory (CDI)	x		
Academic (cognitive) skills	Reading, writing and mathematics		x	
Class socio-emotional skills	Specific questions created for this study		x	
**Teachers**				
Stress and work engagement	Single item stress index		x	
	Bergen Burnout Inventory		x	
	Utrecht Work Engagement Scale (UWES)		x	
Self-efficacy	Teachers’ Sense of Efficacy Scale		x	
	Perceived Collective Teacher Efficacy		x	
	Teacher SEL Beliefs Scale		x	
School environment and leadership	Revised- School Level Environment Questionnaire (R-SLEQ)		x	
	Measure designed for the intervention study		x	
	Global Transformational leadership scale (GTL)		x	
**Teachers and parents**				
Socio-emotional skills	Emotional Self-Efficacy Scale (ESES)		x	x
Teaching style and parenting style	Revised Child Rearing Practices Report Scale (CRPR)		x	x
	Psychological Control Scale		x	x
Teacher-parent interaction and relationship	Family-professional Partnership Scale		x	x
	Trust Scale		x	x

*Only Finnish and Swedish speaking parents.

### Primary outcomes

The children’s *mental health* was measured with the four subscales of the Strengths and Difficulties Questionnaire (SDQ) assessing various psychological problems, such as conduct disorder, hyperactivity, peer relations, and emotional problems with the teachers and parents as raters [17–19]. The Finnish version of SDQ has shown adequate psychometric properties [20–22]. *Socio-emotional skills* were measured with one of the SDQ subscales measuring prosocial behavior and the Multisource Assessment of Social Competence Scale (MASCS) both rated by the parents and the teacher. The MASCS is an instrument designed to measure social competence in the Finnish elementary school context [23] and is partly based on the School Social Behavior Scale (SSBS) created by Merrell and Gimpel [24] for teachers to assess social behavior.

